###### Secondary results

2.3.2.3.2

Evaluation of results in the clinical practice.

-Number of applications to the radiodiagnosis service: the number of applications of abdominal and thyroidal ultrasound scans sent to the radiology service by the physicians in the PCCUC and those in the control group in the year before and the year after the training process will be studied.-Number of referrals to specialized health care: In the same annual periods, the number of referrals by both groups of family physicians will be valued.-Diagnosis waiting times of physicians of the intervention and control groups for 2 processes, which will be used as indicators of healthcare quality improvement (cholelithiasis and the etiological diagnosis of haematuria). The source of data will be the computerized clinical history of the Health Service of Castilla y León.

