### Study population

2.2

The study will include 20 family physicians who want to participate voluntarily, meeting the following inclusion criteria: the practitioners must work in a Spanish primary healthcare center where ultrasonography is available and which belongs to the Health Service of Castilla y León (Sacyl) and to the Health Area of Salamanca; the participants must have a list of over 800 patients; they must have no previous training in clinical ultrasound; and they will have to sign a commitment of attendance and participation in the PCCUC. A control group will be recruited, which will be composed of physicians with similar characteristics in terms of age, sex, workplace, and number of patients assigned. They will be recruited in the first quarter of 2020.

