### Data analysis

2.4

The results will be expressed as mean ± standard deviation for normally distributed quantitative variables or medians (inter-quartile ranges) for biased variables and by distribution of frequency for qualitative variables. For the comparison of qualitative variables, we will use the Chi-squared test or Fisher exact test whenever necessary. To analyze the consistency of the diagnoses, we will use the Kappa test. In the comparison of qualitative variables, we will use the Student *t* test or the Mann–Whitney's *U* test when the conditions of normality of the variable are not met. For the analysis of repeated quantitative before/after data, we will use the Student *t* of paired data or the Wilcoxon test whenever necessary, and the McNemar test for qualitative data. The analysis of the correlation between quantitative variables will be carried out using the Pearson correlation and the Spearman test when the conditions of normality are not met. Lastly, a multivariate analysis will be conducted to determine the factors that produce the best result in the formative process.

The statistical analysis will be carried out using the SPSS v.23.0 software (IBM Corp., Armonk, NY) with the level of statistical significance established at *P* < .05.

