### Methodological limitations

3.1

Since this is a quasi-experimental study with a great variability of the clinical practice of family physicians, it cannot be guaranteed that the differences obtained will be due exclusively to the formative intervention. Likewise, we cannot discard the possibility that a certain degree of Hawthorne effect may occur among the participants. Lastly, the fact that it is impossible to normalize the continuous evaluation at 100% poses a limitation to the objectivity of this result.

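### Diagnosis waiting times: the listed tests are sound on physician-level summaries but not on individual patients, and the plan permits either and names no between-group comparison of change

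*Protocol article*

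**What the plan says.** Section 2.3.2.3.2 (Secondary results) gives the outcome as "Diagnosis waiting times of physicians of the intervention and control groups for 2 processes", the two processes being "cholelithiasis and the etiological diagnosis of haematuria". It adds: "The source of data will be the computerized clinical history of the Health Service of Castilla y León". For radiology applications the same section compares counts "in the year before and the year after the training process will be studied", and referrals use the same annual periods. The periods are not restated for waiting times.

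On numbers, section 2.2 says "The study will include 20 family physicians who want to participate voluntarily". The controls are physicians matched broadly on age, sex, workplace and list size; their number is not given.

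Section 2.4 (Data analysis) is a general list. Between groups it offers Student t or Mann–Whitney (the sentence says qualitative variables, evidently meaning quantitative). For change over time it says "For the analysis of repeated quantitative before/after data, we will use the Student" t for paired data, or Wilcoxon. The one multivariate analysis looks for factors behind a good training result. No test is tied to waiting time, and the section does not say whether the patient or the physician is the unit.

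Section 3.1 describes the design as "a quasi-experimental study with a great variability of the clinical practice of family physicians".

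**The concern.** A waiting time arises once per patient, and each physician contributes several patients. A cholelithiasis or an etiological diagnosis of haematuria is normally made once, so patients diagnosed before the training are almost certainly not those diagnosed after it. The document does not say this; it follows from the nature of a diagnosis.

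If the extracted waits go into the listed tests patient by patient, there are two problems. There are no patient pairs for a paired test. The independent-sample tests treat patients of the same physician as unrelated, so standard errors are too small wherever physicians differ systematically in how quickly their patients reach a diagnosis.

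A third problem does not depend on the unit. The study is a before/after design with a control group, so the question is whether the change differs between groups. A paired test within each group plus a between-group test of the after-period does not answer that.

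The Introduction includes diagnostic waiting time in the evaluation of effectiveness, and section 2.3.2.3.2 uses these two processes as indicators of better care. A false positive here would feed directly into the clinical-benefit claim.

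**Working it through.** **No figure to reproduce.** The article gives no power calculation, standard deviation, intraclass correlation (ICC) or case count for waiting times.

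**Inputs from the article.** 20 intervention physicians (section 2.2); significance level 0.05 (section 2.4).

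**Assumptions.** 20 control physicians; two-sided tests; m = 5 or 10 cases of a process per physician per period; ICC = 0.05, 0.10 or 0.20.

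**Step 1, formula for a patient-level between-group test that ignores physicians.** Design effect DE = 1 + (m − 1) × ICC. Actual two-sided error = 2 × [1 − Φ(1.96/√DE)].

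Example: m = 10, ICC = 0.10. DE = 1 + 9 × 0.10 = 1.9; 1.96/√1.9 = 1.42; error = 0.155.

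**Step 2, simulation under no effect.** Two groups of 20 physicians, two periods with different patients, Poisson case counts with mean m (at least one case), normal outcome, 80% of the physician variance persisting across periods, 4,000 replicates per setting.

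| m | ICC | DE | Error, formula | Error, simulated |
|---|---|---|---|---|
| 5 | 0.05 | 1.20 | 0.074 | 0.077 |
| 5 | 0.10 | 1.40 | 0.098 | 0.101 |
| 5 | 0.20 | 1.80 | 0.144 | 0.167 |
| 10 | 0.05 | 1.45 | 0.104 | 0.115 |
| 10 | 0.10 | 1.90 | 0.155 | 0.166 |
| 10 | 0.20 | 2.80 | 0.241 | 0.261 |

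The simulated values run slightly higher because case counts vary. With Poisson counts the design effect is about 1 + m × ICC. At m = 10 and ICC 0.20 that is 3.0; 1.96/√3.0 = 1.13, giving 0.258, close to the simulated 0.261.

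With fewer cases the problem shrinks. At m = 3 the simulated error is 0.056 (ICC 0.01) to 0.122 (ICC 0.20).

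**Step 3, patient-level before/after comparison within one group.** A paired test cannot be run. An unpaired one gave 0.056 to 0.102 over the six settings in the table; it is less affected because most of the physician effect is common to both periods.

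**Step 4, the listed tests on one mean per physician per period.** This covers m = 3, 5 and 10 and ICC 0.01 to 0.20, twelve settings:
- Paired t within a group: 0.046 to 0.055.
- Independent t on after-period means: 0.045 to 0.053.
- Independent t on physician change scores, between groups: 0.046 to 0.054.

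The simulation standard error at 0.05 is √(0.05 × 0.95/4,000) = 0.0034, so all are compatible with 5%. That the patients differ between years does no harm here, because the pairing is by physician.

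**Step 5, incomplete waits (secondary, conditional).** Suppose cases enter by presentation date, uniformly over a 365-day window, waits are exponential with mean θ, and only waits completed inside the window are analysed. The observed mean is ∫t·f(t)(1 − t/365)dt ÷ ∫f(t)(1 − t/365)dt over 0 to 365, where f is the exponential density. For θ = 120 this is 50.6/0.687 = 74 days; for θ = 80 it is 46.1/0.783 = 59 days. A true difference of 40 days would appear as 15. This illustrates the direction of the bias and does not estimate it for this trial.

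**The case against.** The strongest reply is that the patient-level unit is the reader's own supposition. Physicians are the recruited participants, the other secondary outcomes in the section are counts per physician, and the outcome is worded as belonging to physicians. One value per physician per period is a natural reading, and Step 4 shows that the listed tests then hold their level. Section 2.4 also confines paired tests to repeated data, so it does not prescribe pairing unrelated patients. All of this stands. A reader might infer that the listed tests fit neither the nesting nor the change of patients, and that the P values will be wrong. The document does not support that: it is true only if patients are the unit, which the document neither states nor excludes.

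A reader might also infer that patients with haematuria still undiagnosed at year end will be dropped. That is not supported either. The article gives no start or end point for the wait, no rule for open cases, and no explicit window for this outcome. Such definitions are commonly left to a fuller document.

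The variability mentioned in section 3.1 concerns attributing differences to the training. It makes a non-zero ICC plausible but gives no value for one.

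The remaining reply, that an unseen analysis plan may settle the unit, does not dispose of the point. Section 2.4 does state the methods, and the stated set contains neither a clustered method nor a comparison of change between groups.

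**Conclusion.** The point holds in conditional form. With individual patients as the unit, which the plan permits, paired tests are inapplicable and a between-group t test has a type I error of roughly 7% to 26%. That range assumes ICC 0.05 to 0.20, 5 to 10 cases per physician per period, 20 controls and a normal outcome. It would be smaller with sparser cases or a lower ICC. With one summary per physician per period, the listed tests are valid.

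Under either unit, the listed methods name no group-by-period contrast, which is what a controlled before/after design calls for. Loss of incomplete waits is a possible further bias that depends on how cases are identified.

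Severity is should-fix: the outcome is secondary, the primary outcome (knowledge and skills) is unaffected, and a valid route already lies within the listed tests.

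**What to change.** Amend section 2.4 for waiting time, separately for each process, in one of two ways:

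- **Physician level.** Compute one waiting-time summary per physician per period, take the before/after change, and compare the changes between groups with the Student t or Mann–Whitney test already listed.
- **Patient level.** Fit a model with group, period and group-by-period terms and physician as cluster; the group-by-period term is the result of interest.

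State that t, Mann–Whitney and paired tests will not be applied to individual patient waits. If cases are entered by presentation date within a closed annual window, treat haematuria still undiagnosed at its end as censored rather than dropping it. The physician summary would then be, for example, a Kaplan–Meier median or the proportion diagnosed within a fixed time.

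The cost is a few sentences, plus presentation dates and open cases from the same clinical record. Confidence intervals will be wider than from a naive patient-level analysis.

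Physicians with no case in a period have no change score. At an average of 3 cases, with Poisson counts, the chance of none in at least one of two periods is 1 − (1 − e⁻³)² = 0.097, about 2 of 20 physicians. If cases prove that sparse, the patient-level model makes better use of the data.

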### Data analysis

2.4

The results will be expressed as mean ± standard deviation for normally distributed quantitative variables or medians (inter-quartile ranges) for biased variables and by distribution of frequency for qualitative variables. For the comparison of qualitative variables, we will use the Chi-squared test or Fisher exact test whenever necessary. To analyze the consistency of the diagnoses, we will use the Kappa test. In the comparison of qualitative variables, we will use the Student *t* test or the Mann–Whitney's *U* test when the conditions of normality of the variable are not met. For the analysis of repeated quantitative before/after data, we will use the Student *t* of paired data or the Wilcoxon test whenever necessary, and the McNemar test for qualitative data. The analysis of the correlation between quantitative variables will be carried out using the Pearson correlation and the Spearman test when the conditions of normality are not met. Lastly, a multivariate analysis will be conducted to determine the factors that produce the best result in the formative process.

The statistical analysis will be carried out using the SPSS v.23.0 software (IBM Corp., Armonk, NY) with the level of statistical significance established at *P* < .05.

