**Methods::**

Quasi-experimental study, with a before/after design, a control group, and 1 year of follow-up. Twenty family physicians working in primary care health centers with a list of over 800 patients will be included, as well as a control group of family physicians with similar characteristics in terms of age, sex, and patient list. A structured training process oriented to the clinical practice of the family physician, primary care clinical ultrasound classroom (AECAP), will be carried out, and the improvement of knowledge and skills of the participants will be evaluated, as well as the improvement of the quality of care based on clinical indicators.

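### Controls are chosen to resemble the trained physicians on age, sex, workplace and list size, but the named between-group tests ignore those variables, which can cost power on the secondary outcomes

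*Protocol article*

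**What the plan says.** **Selection of controls.** Section 2.2 states "The study will include 20 family physicians who want to participate voluntarily" and then "A control group will be recruited", to be "composed of physicians with similar characteristics in terms of age, sex, workplace, and number of patients assigned". The abstract puts it more loosely, as "a control group of family physicians with similar characteristics in terms of age, sex, and patient list", and leaves out workplace. No number of controls, ratio or pairing rule is given, and controls are never described as matched or paired.

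**Outcomes compared with controls.** Section 2.3.2.3.2 compares applications for abdominal and thyroid ultrasound made "by the physicians in the PCCUC and those in the control group in the year before and the year after the training process will be" studied. Referrals over the same annual periods and diagnostic waiting times are also to be assessed in both groups. The primary evaluation of knowledge and skills (2.3.2.3.1) describes no control comparison.

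**Tests.** Section 2.4 names three sets:
- For categorical data: "For the comparison of qualitative variables, we will use the Chi-squared test or Fisher exact test whenever necessary".
- For the next comparison: "we will use the Student *t* test or the Mann–Whitney's *U* test when the conditions of normality of the variable are not met". That sentence begins by referring to qualitative variables, an evident slip for quantitative.
- For repeated measurements: "For the analysis of repeated quantitative before/after data, we will use the Student *t* of paired data or the Wilcoxon test whenever necessary", with McNemar for categorical data.

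The only multivariate analysis looks for factors behind the best training result. It is not described as adjusting the comparison between groups.

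**The concern.** Choosing controls to be alike on variables that drive the outcome removes part of the chance difference between the group means. An unadjusted two-sample test does not credit this, because its standard error still contains all the variation those variables produce.

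The selection variables plausibly matter here. The outcomes include annual counts per physician, which should rise with list size. Lists must exceed 800 patients and have no stated upper limit. Physicians in one workplace also share local access to scanners and radiology.

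What is at stake is sensitivity. With 20 trained physicians, a real reduction in requests or referrals may be missed, or reported with a wider interval than the data warrant. Improved clinical practice is part of the main objective in the Introduction, although these outcomes are listed as secondary.

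**Working it through.** The article gives no sample-size calculation, effect size or correlation, so there is no figure of its own to reproduce.

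**Inputs.** From the article: 20 trained physicians (2.2) and a significance level of 0.05 (2.4). Assumed: 20 controls, a two-sided test, normal outcomes, and effects of 0.5 and 0.9 SD. Also assumed is R², the share of between-physician variance explained by the selection variables, taken from 0 to 0.5.

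**Step 1: standard errors.** With SD σ, the two-sample test uses SE = σ√(2/20) = 0.316σ. If the groups are balanced on the selection variables, the actual SE of the difference is 0.316σ × √(1 − R²). The interval is therefore too wide by a factor of 1/√(1 − R²): 1.12 at R² = 0.2 and 1.41 at R² = 0.5.

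**Step 2: true type I error.** The critical value on 38 df is 2.024, so the error is approximately 2 × P(T₃₈ > 2.024/√(1 − R²)).
- R² = 0.1: 2.024/0.949 = 2.13, giving 3.9%.
- R² = 0.2: 2.024/0.894 = 2.26, giving 2.9%.
- R² = 0.3: 2.024/0.837 = 2.42, giving 2.0%.
- R² = 0.5: 2.024/0.707 = 2.86, giving 0.7%.

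**Step 3: simulation without pairing.** There were 40,000 trials per setting. The controls' mean and SD on one selection variable were set equal to those of the trained group. The adjusted analysis is a regression on group and that variable.

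| R² | Type I error, unadjusted / adjusted | Power at 0.5 SD, unadjusted / adjusted | Power at 0.9 SD, unadjusted / adjusted |
|---|---|---|---|
| 0 | 5.2% / 5.2% | 33.6% / 33.6% | 79.0% / 78.8% |
| 0.1 | 3.9% / 5.0% | 33.2% / 37.1% | 80.4% / 83.1% |
| 0.2 | 3.0% / 5.0% | 32.3% / 41.0% | 82.0% / 87.4% |
| 0.3 | 2.0% / 4.9% | 31.4% / 45.5% | 83.5% / 91.4% |
| 0.5 | 0.7% / 4.9% | 28.5% / 58.7% | 86.5% / 97.6% |

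**Step 4: if controls are individually paired.** With within-pair correlation 0.2, the independent t test has type I error 3.0% and power 32.2% at 0.5 SD, against 38.9% for the paired test. With correlation 0 the paired test is slightly weaker (32.6% against 34.0%), because its critical value on 19 df is 2.093. Mann–Whitney behaves like the t test, with type I error of 3.0% at correlation 0.2 and 0.8% at 0.5.

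**Step 5: comparison of changes.** If a selection variable adds the same amount to a physician's count in both years, it cancels in the year-after minus year-before difference. In the same simulation, a two-sample t test on the change had type I error of 4.9% to 5.0% at every R².

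**The case against.** **Individual matching is not established.** The article describes a group with similar characteristics. A reader might infer that a paired test is required, but the text does not support that. The point survives without pairing, because Step 3 assumes only balance between groups.

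**A before/after contrast may remove the problem.** This is a good objection and it limits the point. A reader might infer that the tests are wrong whatever outcome is analysed, but Step 5 shows otherwise when effects are stable. Correlation would persist on the change only if the selection variables also drive change, for example through a time trend specific to a centre. Section 2.4 does not say whether the between-group test is applied to the change or to the annual count.

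**The P values might be too small.** A reader might infer inflated false positives. That would require trained and control physicians to sit in separate centres. With an invented layout of 5 centres of 4 physicians per group, type I error is 6.8% at an intraclass correlation of 0.05 and 15.9% at 0.30. The article gives no such layout, and section 2.2 makes workplace one of the similarity criteria. The abstract's omission of workplace does not establish separate centres.

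**The loss may be small.** At 0.9 SD and R² of 0.1 to 0.2, adjustment gains only about 3 to 5 points, and the unadjusted test's own power rises with R². Larger losses need a smaller effect or a stronger predictor, and the article gives neither.

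**Adjustment is analysis-plan detail.** This is partly fair, since an unseen plan could add covariates. But section 2.4 does name the tests, and as named they make no use of the way section 2.2 selects controls.

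**Conclusion.** The point holds as a minor one, confined to the secondary outcomes. The named between-group tests do not use the variables on which controls are chosen. If those variables predict annual counts and the counts are compared directly, the unadjusted test is conservative. With 20 controls assumed, adjustment gains about 9 power points (41.0 − 32.3) at an effect of 0.5 SD and R² = 0.2, and nothing at R² = 0. The cost is precision and power, not false positives.

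The size rests on the assumed number of controls, R² and effect, none of which the article states. It also rests on comparing counts rather than stable within-physician changes.

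**What to change.** In section 2.4, make the trained-versus-control comparison of requests and referrals a regression on group with age, sex and list size as covariates. Add health centre as a block where centres contain both groups, or as a cluster term where they do not. Keep the unadjusted Student t or Mann–Whitney test as a sensitivity analysis. State whether controls are individually or group matched, and use a within-pair analysis only if they are individually matched. Say also whether the comparison is of annual counts or of each physician's change.

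The cost is two or three sentences, plus recording each control's centre and any match at recruitment. The covariates are already needed to pick controls, and SPSS can fit the model.

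Three covariates take the df from 38 to 35 and the critical value from 2.024 to 2.030. If they are uninformative and balanced, power at 0.5 SD goes from 33.8% to 33.7%. Chance imbalance on two of them lowered it to about 32% in simulation. Many centre blocks cost somewhat more. Ten centres, as an illustration, would leave 35 − 9 = 26 df, a critical value of 2.056 and power of 33.1% if each centre is evenly split between groups.

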### Design and scope

2.1

This is a quasi-experimental study with a before/after design, a group control and a 1-year follow-up to evaluate the effectiveness of the formative intervention in clinical ultrasound with family physicians. The control group will consist of family physicians with similar characteristics, who will not participate in the AECAP. The project will be carried out with family physicians who work in Spanish primary healthcare centers.

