**Table 1 T1:**
[figure not shown]
Main indications of clinical ultrasound in primary health care.

Therefore, the training of family physicians in clinical ultrasound is a necessary condition for the effective implementation of this tool in primary healthcare centers.^[2]^ Similarly, the new portable devices that, as the future stethoscopes, allow conducting high-quality ultrasound scans using an ultrasound scanner coupled to a Smartphone,^[23,24]^ seem to be designed for use by family physicians and create new possibilities of clinical use both in the doctor's office and at the patient's home.

In the field of primary health care, there are very few studies that value the results of a formative process in clinical ultrasound.^[13]^ This study, as was previously commented, aims to validate a clinical ultrasonography training system for primary healthcare practitioners (AECAP), based on practices with real patients and clinical session methodology; moreover, it is intended to measure certain indicators of consistency, efficiency, and resolving capacity, with a before/after-intervention system using a control group to reinforce the results. We expect that the results obtained in this study will demonstrate the efficacy of the structured training method (PCCUC) and provide arguments in favor of generalizing ultrasonography as a tool of daily use in primary health care.

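### For radiology applications and referrals, the analysis section names no between-group comparison of before-to-after change, although both groups are counted in both years

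*Protocol article*

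**What the plan says.** Section 2.1 (Design and scope) fixes the design: "This is a quasi-experimental study with a before/after design, a group control and a 1-year follow-up". Allocation is not random. Section 2.2 (Study population) states "The study will include 20 family physicians who want to participate voluntarily", and for the comparison group "A control group will be recruited, which will be composed of physicians with similar characteristics in terms of age, sex, workplace, and number of patients". It gives no control group size.

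Section 2.3.2.3.2 (Secondary results) counts applications for abdominal and thyroid ultrasound made "by the physicians in the PCCUC and those in the control group in the year before and the year after the training process". Referrals are counted over the same two annual periods in both groups. Waiting times are to be obtained for both groups, but no before period is given.

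Section 2.4 (Data analysis) allocates tests by type of data:

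- **Before/after quantitative data:** "For the analysis of repeated quantitative before/after data, we will use the Student" test for paired data, or Wilcoxon.
- **Two-sample comparison:** "In the comparison of qualitative variables, we will use the Student" test or Mann–Whitney, with no mention of change or baseline.
- **Multivariate analysis:** aimed at predictors of a good training outcome, with no mention of group, period or baseline.

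The Discussion describes the study as working "with a before/after-intervention system using a control group to reinforce the results".

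**The concern.** When volunteers are compared with non-randomised controls, and both are measured before and after, the controls are useful because they show what would have changed anyway. That information enters only if the change in one group is set against the change in the other, or the after value is compared with allowance for the before value. Section 2.4 names neither.

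The listed tests leave two routes to a conclusion, and each has its own weakness:

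- **A paired test in each group.** A fall in requesting common to all physicians can be significant in the trained group and narrowly miss significance in controls. This pattern is not evidence that the groups differ.
- **A two-sample test on the year-after counts.** A trend common to both groups cancels here, but any difference in requesting habits that existed before training is carried straight into the result.

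At stake is whether a claimed reduction in applications or referrals can be attributed to the training. The Introduction includes clinical-practice results in the main objective, even though section 2.3.2.3.2 labels them secondary.

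**Working it through.** The protocol gives no sample-size calculation, SD or effect size, so there is no figure of its own to reproduce. The check asks how often each route signals an effect when training has none.

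**Inputs from the protocol:** 20 trained physicians (section 2.2); significance at P < .05 (section 2.4).

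**Assumptions:** 20 controls, with 40 as a check; two-sided tests; normal data with SD 1 in each year; before/after correlation ρ of 0.5, 0.7 or 0.8; a change common to both groups of 0, 0.3 or 0.5 SD of the annual value; a baseline difference of 0, 0.3 or 0.5 SD; zero training effect. Simulation used 40,000 replicates per scenario.

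**Route 1: separate paired tests.** The SD of the change is √(2(1−ρ)). Let p be the chance that one group's paired test is significant. With equal, independent groups, the chance of a significant result in the trained group and a non-significant one in controls is p(1−p). This cannot exceed 0.5 × 0.5 = 25%. Results with no baseline difference:

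| ρ | Common change | p | p(1−p) | Simulated | Test of difference in change |
|---|---|---|---|---|---|
| 0.5 | 0 | 0.050 | 0.048 | 0.048 | 0.050 |
| 0.5 | 0.3 | 0.245 | 0.185 | 0.184 | 0.050 |
| 0.5 | 0.5 | 0.568 | 0.245 | 0.247 | 0.050 |
| 0.7 | 0.3 | 0.376 | 0.235 | 0.236 | 0.051 |
| 0.7 | 0.5 | 0.781 | 0.171 | 0.169 | 0.051 |
| 0.8 | 0.3 | 0.525 | 0.249 | 0.253 | 0.050 |
| 0.8 | 0.5 | 0.917 | 0.076 | 0.076 | 0.052 |

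The 0.253 exceeds 25% only through simulation error: √(0.25 × 0.75 / 40,000) ≈ 0.002. The rate rises and then falls, because a large common change is detected in both groups. With 40 controls, ρ = 0.7 and a common change of 0.3 SD, it is 0.126.

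**Route 2: year-after test ignoring baseline.** The SE is √(2/20) = 0.316. A baseline difference of 0.3 SD gives a noncentrality of 0.3/0.316 = 0.95, and 0.5 SD gives 0.5/0.316 = 1.58. Simulated rejection rates were 0.150 to 0.155 and 0.334 to 0.339. With no baseline difference the rate was about 0.05, whatever the common change.

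**Comparator: two-sample test on change.** It rejected in 0.048 to 0.052 of studies across all scenarios.

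**Precision.** The SE of the change contrast relative to the year-after contrast is √(2(1−ρ)): 1.00 at ρ = 0.5, 0.77 at 0.7 and 0.63 at 0.8. Below ρ = 0.5 the ratio exceeds 1, so the change score is then the less precise of the two.

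**The case against.** The strongest reply is that section 2.4 is a generic list in a condensed article. It ties no test to an outcome except kappa to diagnostic consistency. The paired sentence fits the initial and final knowledge test well, the two-sample test could be run on change scores, and the multivariate model could include group. A fuller plan may say so. This has weight: model-level detail is rightly left to such a plan. But section 2.4 does not leave before/after data open. It assigns them to a test that cannot use the control group, and it gives the multivariate analysis a different aim. The limitations section admits that differences may not be due to training alone, but that supplies no contrast.

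Several stronger readings are tempting, and the protocol does not support them:

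- **That quantitative outcomes have no between-group test at all.** The t/Mann–Whitney sentence says *qualitative*, but its condition about normality shows that *quantitative* was meant. It is a slip to correct.
- **That paired tests are wrong throughout.** Section 2.3.2.3.1 describes knowledge testing for participants only. With no control scores, a paired test is the appropriate inferential analysis there.
- **That waiting times are affected in the same way.** No before period is stated for them.
- **That every route credits a common trend to training.** Only the within-group route does.
- **That list size is ignored.** Controls are to be similar in number of assigned patients, and a stable list largely cancels within a physician.

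**Conclusion.** The point holds for two secondary outcomes: applications to radiology and referrals. No stated analysis compares their change between the groups, and the routes that the listed tests offer can produce an apparent training effect where none exists.

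With no training effect and 20 controls, discordant paired tests occur in about 5% of studies with no common change and in at most 25%, depending on the size of the common change. The 25% is a ceiling for equal groups and should not be read as the expected rate. A year-after test rejects in about 15% or 34% of studies at a baseline difference of 0.3 or 0.5 SD. A test of the difference in change stays near 5%.

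Control number, correlation, common change and baseline difference are all assumptions, and the simulation used normal data in place of counts. The figures illustrate the mechanism and do not predict this study's error rate. The point should be fixed. It does not reach the primary knowledge and skills results, which limits its severity.

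**What to change.** In section 2.4:

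1. State that for applications and referrals the effect estimate is the between-group difference in before-to-after change, with its 95% CI. A group-by-period term, a baseline-adjusted model or a two-sample test on change scores would each serve. A count model with assigned patients as offset is one suitable option, not a requirement.
2. Choose one in advance, because the options can disagree when groups differ at baseline. If the groups differ by a stable amount and follow parallel trends, adjustment for baseline leaves (1−ρ) of the difference in the estimate: at ρ = 0.7 and 0.5 SD, 0.3 × 0.5 = 0.15 SD. The near-5% rate above was shown for the change contrast.
3. Make within-group paired tests descriptive for these two outcomes only.
4. Apply the same contrast to waiting times if before-period data are collected.
5. Keep the paired test as the inferential analysis of the initial and final knowledge test.
6. Correct *qualitative* to *quantitative* in the t/Mann–Whitney sentence.

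The cost is a few sentences. Applications and referrals are already to be counted in both groups and both years, and a two-sample test on change stays within the listed methods. An offset would also need each physician's list size for each year, which section 2.3.2.3.2 does not list.
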